### Participant timeline {13}

Besides the section presenting outcomes above ({12}), a flow chart for the trial is presented in Fig. 1, and a time schedule for the trial is presented as a schematic diagram in Table 1.

**Fig. 1 Fig1:**
[figure not shown]
Flow chart for the trial

**Table 1 Tab1:** Time schedule for the trial

	**Trial period**							
	**Enrolment**	**Post-allocation**						**Follow-up**
**Timepoint**	*0 h*	*6 h*	*12 h*	*24 h*	*36 h*	*48 h*	*72 h*	*Days 90 and 180*
**Enrolment**								
**Eligibility screen**	x							
**Informed consent**	Trial guardian and next of kin							Patient as soon as possible
**Randomization**	x							
**Interventions**								
**Infusion of study drug**	x							
**Assessments**								
**Biochemistry**^**a**^	x	x	x	x	x	x	x	
**Biobank samples**	x			x		x	x	
**ECG**	x	x	x	x	x	x	x	
**Swan-Ganz-based measurements**	x	x	x	x	x	x	x	
**Echocardiography**				Day 1				Before discharge
**ABG and VBG**^**b**^	x	x	x	x	x	x	x	
**SOFA score**				x		x	x	
**CPC and mRS score**								x
**MoCA score**								Only day 90

*ABG* Arterial blood gas, *CPC* Cerebral Performance Category, *ECG* Electrocardiogram, *mRS* Modified Rankin Score, *MoCA* Montreal Cognitive Assessment, *SOFA* Sequential Organ Failure Assessment, *VBG* Venous blood gas

^a^Details in outcomes section in the manuscript

^b^Additional blood gasses are taken bihourly until 12 h and at 18 h

### Sample size {14}

The trial is powered at the co-primary endpoint. We chose a priori to power the trial at the “weakest” of the two endpoints, ensuring that we would have sufficient power for both endpoints. As we were not able to find data regarding the effect of methylprednisolone on IL-6- or NSE levels from admission, we chose to power the trial towards a single measurement drawn 48 h after admission. With the assumption that methylprednisolone would reduce IL-6 levels by 20%, the trial would achieve a power of 0.90 at an alpha-level of 0.025 if 112 patients were included. With the assumption that methylprednisolone would reduce NSE levels by 20%, the trial would achieve a power of 0.90 at an alpha-level of 0.025 if 114 patients were included.

Based on the above, inclusion of 120 patients would be sufficient to adjust for missingness due to withdrawn consent, though we estimated from previous studies that approximately 20% of resuscitated OHCA patients would die within 72 h, i.e., before complete assessment of the co-primary endpoint. Further, due to the acute nature of the trial, we expect 10% of post-randomization exclusions and/or patients where consent is not obtained. To achieve a complete set of blood samples from 120 patients, we, therefore, plan to include 1.30 × 120 = 156 patients. We will however stop the trial before if our target at 120 patients is reached.

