#### Hypothesis

Bolus infusion of 250 mg methylprednisolone in the pre-hospital setting will inhibit the systemic inflammatory response and reduce biomarkers of the degree of cerebral injury in comatose, resuscitated OHCA patients.

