### Outcomes {12}

#### Primary outcome

The primary outcome is the repeated daily measurements of IL-6 and NSE at admission and the following 24, 48, and 72 h after admission.

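### IL-6 and NSE are each sized at alpha 0.025 with no step that passes alpha on; if they are tested that way, Holm gives more power at the same family-wise error

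*Protocol article*

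**What the plan says.** The Primary outcome section names two biomarkers: "The primary outcome is the repeated daily measurements of IL-6 and NSE at admission" and daily to 72 h. Sample size {14} calculates for each separately, on a single 48 h measurement and an assumed 20% reduction. IL-6 is given "a power of 0.90 at an alpha-level of 0.025 if 112 patients were included"; for NSE, "the trial would achieve a power of 0.90 at an alpha-level of 0.025 if 114 patients were included". The section says the trial was powered on the weaker of the two, "ensuring that we would have sufficient power for both endpoints". The target is 120 patients with complete samples.

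The Hypothesis section expects an effect on both fronts: the drug "will inhibit the systemic inflammatory response and reduce biomarkers of the degree of cerebral injury".

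Statistical methods {20a} specifies linear mixed models for the co-primary endpoint. Neither that section nor the missing-data section {20c} gives a significance level or a multiplicity rule, or says whether one marker or both must succeed. The 0.025 in Sample size {14} is therefore the only significance level in the article.

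**The concern.** With two primary markers, 0.025 for each looks like an equal Bonferroni division of 5%. That is valid, but it leaves error rate unused: once one marker is significant at 0.025, the other can be tested at 0.05 without pushing the family-wise error above 5%. Under a flat division, a marker with p = 0.03 would count as negative even when the other is clearly positive, and nothing is gained in error control.

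The trial asks about inflammation and about brain injury, so the chance of showing both effects matters. That chance is lower than the 0.90 quoted for each marker, and it is where the flat division costs most.

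**Working it through.** **Inputs.** From Sample size {14}: alpha 0.025 and power 0.90 per marker, 112 patients (IL-6), 114 patients (NSE), target 120. From Trial design {8}: 1:1 allocation. Assumed, because the article does not give them: two-sided tests, and a correlation of 0 to 0.5 between the two test statistics.

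**The plan's own figure.** The 112 and 114 cannot be reproduced independently, because no standard deviation is given. Back-solving the two-means formula gives standardised effects of 2 × 3.523/√112 = 0.666 and 2 × 3.523/√114 = 0.660. With a 20% reduction (log 0.8 = −0.223) these imply a log-scale SD of about 0.335 to 0.338. The comparison below does not depend on that SD.

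**Per-marker power.** At 0.90 power and two-sided 0.025, the expected test statistic is z(0.9875) + z(0.90) = 2.241 + 1.282 = 3.523. The same statistic tested at 0.05 has power Φ(3.523 − 1.960) = 0.941.

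**Independent markers, by hand.**
- Flat 0.025, both significant: 0.90² = 0.810.
- Holm, both significant: both p-values below 0.05, less the case where both lie between 0.025 and 0.05: 0.941² − (0.941 − 0.900)² = 0.8854 − 0.0017 = 0.884.
- Holm, a given marker significant: 0.900 + (0.941 − 0.900) × 0.900 = 0.937.
- At least one significant, either rule: 1 − 0.10² = 0.990.

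**Correlated markers**, from the bivariate normal distribution, each marker at its stated 0.90:

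| Correlation | Both, flat | Both, Holm | Each, Holm | At least one (either rule) |
|---|---|---|---|---|
| 0 | 0.810 | 0.884 | 0.937 | 0.990 |
| 0.3 | 0.822 | 0.889 | 0.933 | 0.978 |
| 0.5 | 0.832 | 0.894 | 0.931 | 0.968 |
| 0.8 | 0.856 | 0.905 | 0.925 | 0.944 |

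**At the 120 target.** The expected statistics become 3.523 × √(120/112) = 3.647 and 3.523 × √(120/114) = 3.614. Power at 0.025 is then 0.920 for IL-6 and 0.915 for NSE. Joint power goes from 0.842 (flat) to 0.906 (Holm) at correlation 0, and from 0.860 to 0.913 at correlation 0.5, a gain of 5 to 6 points.

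**Error control.** Holm holds family-wise error at 5% under any correlation. Simulation with 2 million draws at correlations 0 to 0.5 gave 0.047 to 0.050 with no true effect on either marker, and 0.045 to 0.048 with an effect on one only.

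**If both markers were required for success**, each could be tested at 0.05 with no division of alpha. Joint power at the planned sizes would be 0.885 (correlation 0) to 0.897 (correlation 0.5).

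**The case against.** The strongest reply is that the article states no final testing rule. The 0.025 is a sizing input, and the methods sections are silent on multiplicity. A trial that will use Holm may be sized at 0.025 per marker, since that is Holm's first step, and the analysis plan, which is not shown, may already name such a rule. This stands in part. A reader might infer that the protocol prescribes Bonferroni and would declare p = 0.03 negative; the article does not say so. The point is conditional: it applies if the only level given is also the level used.

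A reader might also infer that the flat level is inferior on every reading. The text does not support that either, because "at an alpha-level of 0.025" leaves sidedness open. If 0.025 is one-sided, each marker is already at the equivalent of two-sided 0.05, and nothing is lost if both markers are required. If it is half of a one-sided 0.05, the gain is much as above: joint power 0.81-0.83 to 0.89-0.90.

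Nor is the 0.90 wrong. It is a per-marker figure and the article never claims joint power of 0.90.

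Three further replies limit the size. A flat division is valid and gives simple simultaneous confidence intervals. The correlation is assumed. And Statistical methods {20a} expects the mixed model to give more power than the single-measurement calculation. If per-marker power were 0.95 (an assumption), independent markers would give joint power of 0.903 flat and 0.946 with Holm, a gain of about 4 points; at 0.975 the gain is about 2 points. These reduce the gain but do not reverse the ordering, because Holm rejects whenever the flat division does.

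**Conclusion.** The point holds as a conditional improvement in efficiency; it is not an error of validity. If IL-6 and NSE are each tested at a flat two-sided 0.025, the trial gives up 6 to 7 points of joint power at the planned 112/114, or 5 to 6 points at 120, and 3 to 4 points per marker at the planned sizes, with no gain in error control. Power to show an effect on at least one marker is unaffected. The figures rest on the stated 0.90 per marker, two-sided testing, a correlation of 0 to 0.5, and the single 48 h measurement used for sizing. At correlation 0.8 the joint gain at the planned sizes is about 5 points (0.856 to 0.905).

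**What to change.** Before unblinding, state in the statistical methods whether a win on either marker counts as success or both are required.
- If either counts: test IL-6 and NSE by Holm at an overall two-sided 0.05, the smaller p-value against 0.025 and, if significant, the other against 0.05.
- If both are required: test each at 0.05.

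If the analysis plan already has a rule, align the article with it. In the sample-size section, give the sidedness, make clear that 0.90 is power per marker, and preferably add the joint figure with its assumed correlation.

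The cost is a sentence or two, with no extra patients or data. The one small drawback is that simultaneous confidence intervals matching Holm are less simple than those matching a flat division.

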**Methods:**

The study is an investigator-initiated, randomized, multicenter, single-blinded, placebo-controlled, clinical trial. Inclusion will continue until one hundred twenty unconscious OHCA patients surviving a minimum of 72 h are randomized. Intervention is a 1:1 randomization to an infusion of methylprednisolone 250 mg following a minimum of 5 min of sustained return of spontaneous circulation in the pre-hospital setting. Methylprednisolone will be given as a bolus infusion of 1 × 250 mg (1 × 4 mL) over a period of 5 min. Patients allocated to placebo will receive 4 mL of isotonic saline (NaCl 0.9%). Main eligibility criteria are OHCA of presumed cardiac cause, age ≥ 18 years, Glasgow Coma Scale ≤ 8, and sustained ROSC for at least 5 min. Co-primary endpoint: Reduction of interleukin-6 and neuron-specific-enolase. Secondary endpoints: Markers of inflammation, brain, cardiac, kidney and liver damage, hemodynamic and hemostatic function, safety, neurological function at follow-up, and mortality. A research biobank is set up with blood samples taken daily during the first 72 h from hospitalization to evaluate primary and secondary endpoints.

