#### Participant retention and follow-up plan {18b}

Patients included are expected to remain in the ICUs the first three days of admission until the primary endpoints are collected. If a patient awakes and is transferred to the ward, blood sampling will be done here, including samples for the research biobank to analyze the primary endpoints. If a patient is transferred to a local hospital within three days of admission, samples for the biobank are not taken but standard biochemistry will be taken routinely and will be collected. At both sites, dedicated staff will be responsible for follow-up in the ambulatory setting at approximately 90 days following OHCA. The patient will be offered a visit at home if an ambulatory visit is not possible or not wanted by the patient. Patients who discontinue the study during follow-up will remain in the study database if an informed consent is obtained. After 180 days patients will be evaluated through a telephone interview.

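### The enrolment figure of 156 multiplies by 1.30 instead of dividing by the retained share, so it yields about 109 to 112 complete sample sets, not 120

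*Protocol article*

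**What the plan says.** All the inputs are in Sample size {14} of the protocol article.

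- **Power requirement.** It is set for one sample at 48 h. IL-6 needs 112 patients. For NSE, a treatment that would "reduce NSE levels by 20%, the trial would achieve a power of 0.90 at an alpha-level of 0.025 if 114 patients were included". The larger of the two, 114, governs, and the target is set at 120.
- **Losses.** The section expects that "approximately 20% of resuscitated OHCA patients would die within 72 h, i.e., before complete assessment of the co-primary endpoint". It adds that "we expect 10% of post-randomization exclusions and/or patients where consent is not obtained".
- **Enrolment.** "To achieve a complete set of blood samples from 120 patients", the authors "plan to include 1.30 × 120 = 156 patients", and they will stop sooner if the target of 120 is met.

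Two other places bear on the yield. The Methods paragraph of the abstract says "Inclusion will continue until one hundred twenty unconscious OHCA patients surviving a minimum of 72 h are randomized" and does not mention 156. Participant retention and follow-up plan {18b} says: "If a patient is transferred to a local hospital within three days of admission, samples for the biobank are not taken".

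**The concern.** A loss rate of 20% or 10% describes a fraction of those who enter the trial. Adding 30% of the target to the target covers a loss of 30% of 120, which is 36 patients. The expected loss is 28% to 30% of 156, which is about 44 to 47. The inflated number therefore cannot deliver the target it was built for.

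What is at stake is mainly the credibility of the stated enrolment. The margin of six patients between 114 and 120 was meant as a reserve. On the article's own assumptions that reserve is used up, and the expected number of complete sets is below 114 as well. The effect on power is a secondary matter and is small.

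The definition of the target adds to the difficulty. The abstract counts patients who survive 72 h, whereas the sample size section counts patients with complete samples. Once 156 is seen to fall short of 120 complete sets, it matters which unit closes recruitment and whether 156 is an upper limit.

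**Working it through.** **Inputs** (all from Sample size {14}): target T = 120 complete sets; deaths by 72 h 20%; exclusions or missing consent 10%; NSE requirement 114 at power 0.90 and alpha 0.025; IL-6 requirement 112 at the same power and alpha. Allocation is 1:1 (Trial design {8}).

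**1. The plan's own figure.** T × (1 + 0.20 + 0.10) = 120 × 1.30 = 156. This reproduces exactly, so the method used is multiplication by one plus the loss.

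**2. Retained share.** The article does not say how the two losses combine, so both readings are shown.
- Added: 1 − 0.20 − 0.10 = 0.70
- In sequence: 0.80 × 0.90 = 0.72

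**3. Yield and required enrolment** (required figures rounded up).

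| | Retained 0.70 | Retained 0.72 |
|---|---|---|
| Complete sets from 156 | 156 × 0.70 = 109.2 | 156 × 0.72 = 112.3 |
| Enrolment for 120 sets | 120/0.70 = 171.4, so 172 | 120/0.72 = 166.7, so 167 |
| Enrolment for 114 sets | 114/0.70 = 162.9, so 163 | 114/0.72 = 158.3, so 159 |
| P(at least 120 of 156), binomial | 0.034 | 0.099 |
| P(at least 114 of 156), binomial | 0.23 | 0.42 |

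For 156 to give 120, total loss would have to be 1 − 120/156 = 23.1%, against the 28% to 30% stated.

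**4. Single-sample power.** No standard deviation is given, so the 112 and 114 cannot be rebuilt. The standardized difference d is instead solved from the stated NSE result and carried to other sizes by the normal approximation, power = Φ(d√(N/4) − z), where N is the total and z the critical value. The article does not state whether alpha is one- or two-sided.
- Two-sided 0.025: d = (2.241 + 1.282) × √(4/114) = 0.660. Power is 0.886 at N = 109, 0.894 at 112, 0.900 at 114 and 0.915 at 120.
- One-sided 0.025: d = 0.607. Power is 0.887 at 109, 0.895 at 112 and 0.914 at 120.
- IL-6, solved from 112 in the same way: about 0.891 at 109 and 0.900 at 112, two-sided.

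The loss on NSE is therefore about 0.5 to 1.5 percentage points.

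**5. The abstract's count.** If only deaths are removed, 156 × 0.80 = 124.8 survivors are expected, and the binomial chance of at least 120 is about 0.86.

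**The case against.** The strongest reply is that the slip has little consequence, and much of that reply stands.

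- **Unlike quantities.** The 114 is a requirement for one sample at 48 h, whereas 109 to 112 counts series complete to 72 h. A patient who dies between 48 h and 72 h can still supply the 48 h value. As far as the two stated losses go, 109 to 112 is a lower bound on the usable 48 h samples.
- **The planned analysis.** Statistical methods {20a} specifies linear mixed models on the repeated measurements, which can use partial series. It expects more power than the single-sample calculation gives, although it shows no figure for the gain.
- **Scale.** A change of about one point matters little in a phase II trial whose 20% effect is itself an assumption and whose Discussion calls its results hypothesis-generating.

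A reader might infer from the shortfall that the trial is underpowered, with an expected NSE power of 0.885 to 0.895. For the first two reasons, the document does not support that.

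A reader might also infer that the abstract and the sample size section give stopping rules that flatly conflict. This too goes too far. On the abstract's count of 72 h survivors, 156 patients reach 120 about 86% of the time, and the sample size section never says in terms that 156 is a maximum. The real difference is in what is counted.

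Finally, transfer to a local hospital could lower the yield, but no rate is given. Section {18b} also expects patients to stay in the ICU for the first three days and continues sampling on the ward, so the size of this loss is unknown.

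None of this rescues 156 as the number for its stated purpose. That purpose is complete samples from 120 patients, and neither reading of the losses gets there.

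**Conclusion.** The stated enrolment is wrong for its stated goal. With the article's own loss rates, 156 patients are expected to give about 109 to 112 complete sample sets. That is 8 to 11 short of 120 and 2 to 5 short of 114, and 167 to 172 would be needed for 120. This rests on reading both percentages as shares of patients included, which is how the article words them. The binomial probabilities also assume independent losses at exactly the stated rates.

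The effect on power is minor. The NSE range of roughly 0.885 to 0.895 depends on a standardized difference solved from the stated 114. It is a floor for the two stated losses under a single-sample test. The unit of the target and the status of 156 are a linked point of clarity. Transfer losses are an unquantified further risk to the yield. Should-fix.

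**What to change.** In Sample size {14}, do one of the following:

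1. Replace the calculation by division, and state that about 167 (losses in sequence) to 172 (losses added) patients would be randomized for 120 complete sets.
2. Keep 156 and state that about 109 to 112 complete sets are expected. If power is mentioned, describe 0.885 to 0.895 as a single-sample lower bound for NSE on the two stated losses, not as the expected power of the mixed-model analysis.

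In the abstract and in Sample size {14}, use the same unit for the target of 120, either 72 h survivors or complete sample sets, and say whether 156 is a cap. Add a sentence that transfers within three days may reduce the number of complete sets, with a rate if one is known.

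The second option costs only wording and needs no further patients. The first adds 11 to 16 patients to the planned figure (167 − 156 and 172 − 156).

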### Recruitment {15}

The study includes an enrolment period of up to 18 months, followed by a follow-up period of 6 months and analyses of paraclinical results another 12 months. The expected study period is based on previous clinical studies in OHCA patients at our department, where approximately 150 patients are included each year (including OHCA patients admitted from outside the Capital Region of Denmark).

## Methods: assignment of interventions

### Allocation {16}

#### Sequence generation {16a}

The pharmacy of the Capital of Region of Denmark will prepare, box, and label the study medicine and the placebo ampoules. The pharmacy is approved by the Danish Health authorities. Randomization will be generated by using the website randomization.com (http://www.randomization.com) with allocation in a 1:1 fashion with active study medicine and placebo randomized in permuted blocks of four. The pharmacy will be responsible for generation of the allocation sequence. Study medicine and placebo are placed in identical opaque boxes and will be numbered randomly according to allocation. Once prepared the pharmacy will ship twenty boxes to the five “physician staffed CCU” stations covering the Capital Region of Denmark. The CCUs are manned 24 h 7 days a week with a physician (henceforth referred to as “CCU physician”) and an experienced paramedic. The responsible project physician will ensure that any CCU station always has boxes in storage and ready for use, and when box storage is used, the pharmacy will provide new boxes. Before each shift, the on-duty physician and paramedic will make sure that a minimum of two boxes are stored in their unit. When a patient is successfully screened the including physician will open one of these boxes and use the content (study medicine or placebo). The box number will be registered by the including physician and for safety reasons a photo of the box number will be taken to the pre-hospital journal and the empty box will be delivered to the department at hospital admission. All treating in-hospital personnel and study coordinators will remain blinded throughout the study. Still, in case of need for emergency unblinding, this can be done by the principal investigator at each site.

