#### Concealment mechanism {16b}

Treatment allocation is managed as described above. The opaque boxes containing study medicine or placebo are identical besides the assigned unique allocation ID written on the box. Treatment assignment during the trial is only available for the including CCU physician and the accompanying medical assistant manning the CCU following screening of the patient and contact with the trial guardian for informed consent. Once informed consent is obtained, the including physician opens a random opaque box and infuse the content, i.e., study medicine or placebo. The box allocation number will be available at all time through information filled out in the pre-hospital journal, consent by the including physician and/or the delivery of the used box at the department of admission.

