### Blinding {17}

#### Who will be blinded {17a}

All in-hospital personnel, research personnel, and patients will be blinded to intervention allocation throughout the trial. The including pre-hospital CCU physician and the medical assistant will be blinded during screening, inclusion, and randomization of the patient, but unblinded upon breaking concealment of the randomized box. Infusion is completed before arrival at the hospital and no information other than allocation number will be given at hospital admission. When follow-up is completed, and data collected, the database will be locked and treatment allocation will be unblinded.

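### A single block size of four, with enrolling crews who learn each allocation and no set box order, lets a crew that keeps a tally guess later allocations better than chance

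*Protocol article*

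**What the plan says.** All of this is in the protocol article.

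- **Sequence generation {16a}.** The pharmacy generates the list with "allocation in a 1:1 fashion" and "active study medicine and placebo randomized in permuted blocks of four". No other block size is mentioned. The boxes "will be numbered randomly according to allocation". On supply, "the pharmacy will ship twenty boxes to the five" physician-staffed stations, which can be read as 20 in total or 20 each. Each shift checks that "a minimum of two boxes are stored in their unit", and after screening "the including physician will open one of these boxes and use the content".
- **Concealment mechanism {16b}.** Boxes are opaque and identical except for their ID. After consent, "the including physician opens a random opaque box and infuse the content". No order of opening is given.
- **Who will be blinded {17a}.** The physician and assistant are blinded up to randomization, then "unblinded upon breaking concealment of the randomized box". Hospital staff, research staff and patients stay blinded.
- **Eligibility criteria {10}.** Screening is done by the on-duty physician of the mobile unit, the same role that opens the boxes.

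**The concern.** Concealment protects a trial only while the person judging eligibility cannot anticipate the next allocation. Here that person's role sees the content of every box it opens, and the block size is small and fixed. Past openings at a station therefore carry information about the boxes that remain.

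Several eligibility criteria are roadside judgements: presumed cardiac cause, a GCS of 8 or less, known limits on therapy. A crew with a view on what comes next could, without intending it, be readier to enrol one kind of patient than another. The background section describes IL-6 and NSE as markers of poor outcome, so selection by severity would act directly on both co-primary endpoints, for which the assumed effect is a 20% reduction. The infusion ends before hospital arrival and the first sample is taken at admission, so no pre-dose biomarker value is listed that could reveal such selection.

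A second, smaller matter is internal consistency. Section {16a} has the pharmacy build a blocked sequence, and {16a} and {16b} then leave the order of use to a pick on the spot.

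**Working it through.** The article gives no predictability figure, so there is none to reproduce. The inputs are the block size of four, the 1:1 ratio, 20 boxes and five stations (all {16a}), 156 planned patients (Sample size {14}) and up to 18 months of enrolment (Recruitment {15}).

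**Guessing rule.** The observer names the arm opened less often so far and tosses a coin when the arms are level (the Blackwell-Hodges convergence strategy). For a balanced stock of 2m boxes used to the end, the expected share of correct guesses is

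[m + (2^(2m)/C(2m,m) − 1)/2] / (2m).

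**(a) One block of four per station** (20 boxes over five stations, 20/5 = 4 each), m = 2:
- [2 + (16/6 − 1)/2]/4 = 2.833/4 = 70.8% correct.
- Check by listing the six possible orders: the chance of a correct guess at positions 1 to 4 is 1/2, 2/3, 2/3 and 1, which sums to 2.833.
- Fully determined: the fourth always and the third with probability 1/3, so (1/3 + 1)/4 = 33.3%.

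**(b) Twenty balanced boxes per station, picked freely**, m = 10:
- [10 + (1,048,576/184,756 − 1)/2]/20 = 12.338/20 = 61.7% correct.
- Fully determined (simulation): 9.1%.
- Share of sets of four consecutive openings that are 2:2: C(10,2)²/C(20,4) = 2,025/4,845 = 41.8%, against 100% if whole blocks are used in order.
- The running imbalance exceeds 2 in 78.7% of simulated stocks. It cannot exceed 2 when blocks of four are used in order.

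**(c) Twenty balanced boxes dealt at random, four per station, the crew knowing only its own station:**
- Chances at positions 1 to 4: 0.500, 10/19 = 0.526, 0.526, 0.542. The sum is 2.094, and 2.094/4 = 52.4% correct.

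| Reading of the supply | Correct guesses | Fully determined |
|---|---|---|
| (a) one block per station | 70.8% | 33.3% |
| (b) 20 mixed boxes per station | 61.7% | 9.1% |
| (c) random deal, four per station | 52.4% | not computed |
| chance | 50% | 0% |

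**Opportunity.** 156/5 = 31.2 patients per station, and 31.2/18 = 1.7 per station per month.

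**Effect of varying block sizes**, used in order at a station over a run of 30 patients (simulation):

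| Block sizes | Correct guesses | Fully determined |
|---|---|---|
| 4 only | 70.0% | 31% |
| 4 and 6 | 68.8% | 6% |
| 4, 6 and 8 | about 67% | about 2% |

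The determined share is for an optimal guesser who knows which sizes are in use. For block size 4 it is 31% rather than 33.3% because a run of 30 ends in mid-block. Varying the sizes removes near-certainty but barely reduces guessing by tally.

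**The case against.** The strongest reply is that 71% is the top of a range and needs two things the article does not state: that each station holds exactly one block, and that whoever screens knows every box opened there. Units run round the clock in shifts, each allocation is seen only by the physician and assistant present, the empty box travels to the hospital with the patient, and enrolment is under two patients per station per month. No shared tally is described. Stations are also resupplied, which may mix blocks. This stands, and it is why the size is given as 52% to 71%.

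There are also safeguards. A guardian doctor outside the patient's treatment must consent before the box is opened, the national arrest registry serves as screening log, so enrolment can be checked afterwards, and the enrolling physician takes no further part in care. The endpoints are laboratory values collected under blinded hospital care. These limit selection but do not remove it.

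Four stronger readings are tempting and do not hold:

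- *That the physician can steer a patient to an arm.* Unopened boxes are indistinguishable, so the pharmacy's packing decides the content. Only the decision to enrol is exposed.
- *That both harms occur in full together.* They trade off. With one block per station, guessing is easiest but free picking leaves the 2:2 balance intact. With mixed stock the blocks break and guessing is harder.
- *That crews knew the block size because it was published.* The article is dated November 2022, after the estimated end of recruitment in July 2022. Strategies to improve adherence {11c} says physicians were given the study protocol, but that document is not shown, so whether it states the block size is unknown.
- *That bias occurred.* Nothing in the article shows this.

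**Conclusion.** The point holds as a moderate weakness in concealment. The three premises are in the text: one fixed block size, enrolling crews unblinded at each opening, and no prescribed order. A crew that keeps a tally would guess correctly in about 52% to 71% of cases, with up to one third of allocations certain at the upper end. The range assumes a crew that knows all openings at its own station. A crew without that knowledge has correspondingly less advantage. If a station's stock mixes blocks, the blocked order is also not followed, although that mainly affects balance and is the lesser matter. Outcome assessment is not directly affected.

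**What to change.** **For boxes still to be shipped**, all at the pharmacy plus one line on the crews' pocket card:

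1. Generate the sequence with randomly varying block sizes, for example 4, 6 and 8, and do not disclose them to crews.
2. Send each station stock that does not coincide with whole blocks, and state how blocks map to stations. This matters as much as step 1, because varying sizes alone lowers tally guessing only from about 70% to 67%. Case (c) shows how far it can fall when a station's stock is not a balanced set.
3. Number the boxes in sequence order and require the lowest number in the unit to be opened first. With numbers assigned at random, opening the lowest first would not restore the sequence.

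Step 3 should not be adopted without step 2. If stations in fact hold 20 mixed boxes, ordered use of small blocks (about 67%) is more guessable by tally than free picking (61.7%), although fewer allocations are certain (about 2% against 9.1%).

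**If recruitment has ended**, which the estimated dates suggest, compare the recorded box numbers with the pharmacy list, state how blocks were distributed to stations, and report any departure from blocked order.

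The cost is small. The arms may end slightly less even: within a block of eight the imbalance can reach 4, against 2 in a block of four.
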